|  | Study informed consent |  | X |  |  |  |
|  |  |  |  |  |  |  |
| **II. Enrollment & Study ID** | Study ID number assignment |  | X |  |  |  |
|  | Patient registration in Register |  | X |  |  |  |
|  | Patient file creation |  | X |  |  |  |
|  | Patient appointment card |  | X |  |  |  |
|  |  |  |  |  |  |  |
| **III. Physical Measurements** | Height |  | X |  |  |  |
|  | Weight |  | X | X | X | X |
|  | Waist circumference |  | X |  | X | X |
|  | Blood pressure |  | X | X | X | X |
|  | 7-day pedometer steps |  | X |  |  | X |
|  |  |  |  |  |  |  |
| **IV. Biochemical** | FPG (Uganda & South Africa) | X, X | X | X | X | X |
|  | HbA1c (All sites) |  | X |  |  | X |
|  |  |  |  |  |  |  |
| **V. Basic participant data** | Pre-eligibility assessment | X |  |  |  |  |
|  | Eligibility confirmation |  | X |  |  |  |
|  | Eligibility and recruitment check |  | X |  |  |  |
|  | Contact Information |  | X |  |  |  |
|  | Demographic and social measures |  | X |  |  |  |
|  | Medical and medication history |  | X |  |  |  |
|  | Behavioral measures (diet, physical activity, foot care, tobacco use, alcohol consumption) |  | X |  |  | X |
|  |  |  |  |  |  |  |
| **VI. Intervention process measures** | Participant diabetes knowledge |  | X |  |  | X |
|  | Illness perception |  | X |  |  | X |
|  | Social support and sources of support |  | X |  |  | X |
|  | Self-efficacy, autonomy support & self-regulation |  | X |  |  | X |
|  | Psychological adjustment |  | X |  |  | X |
|  | Quality of life & Stress |  | X |  |  | X |
|  | Diabetes treatment satisfaction |  |  |  |  | X |
|  | Out of pocket expenditure |  |  | X | X | X |
|  | Incremental cost to the health facility |  |  | X | X | X |
|  | Adherence to study procedures and to intervention elements |  | X |  |  | X |
|  |  |  |  |  |  |  |
| **VII. Facility forms** | Process evaluation |  |  | X | X | X |
|  |  |  |  |  |  |  |
| **VIII. Community forms** | Environment context measurement (EPOC) |  | X |  |  |  |

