## 3.9 Outcomes of interest:

*Primary outcomes of interest*

Among participants with pre-diabetes, the primary outcome of interest will be reduction in plasma glucose between baseline and month 12 of follow-up. We hypothesize that participants with pre-diabetes in the facility + community arm will on average have a higher reduction in their HbA1c reading by the end of follow-up compared to participants with pre-diabetes in the facility alone arm, and the current practice arm in Uganda.

Regarding participants with type 2 diabetes, research has shown that, reduction of HbA1c level by 1% among such individuals leads to: a) 19% less likelihood of cataracts, b) 16% less likelihood of heart failure, and c) 43% less likelihood of amputations or death due to peripheral vascular disease [Anon 1993]. Further the UK Prospective Diabetes Study (UKPDS) [King et al 1999], and the Diabetes Control and Complications Trial (DCCT) demonstrated that improving HbA1c by 1% for people with type 1 diabetes *or* type 2 diabetes cuts the risk of microvascular complications by 25%. Therefore among participants with diabetes, the primary outcome of interest will also be reduction of their plasma glucoce levels. A participant will be classified as having had their plasma glucose reduced if:

1. Their HbA1c reading at month 12 is reduced to below 53 mmol/mol, or
2. Their HbA1c reading at month 12 is 5 mmol/mol below their baseline reading.

*Secondary outcomes of interest*

Secondary outcomes in this trial will include:

a) Incidence of diabetes among participants with pre-diabetes

b) Incidence of conversion from a state of pre-diabetes to normal plasma glucose levels.

c) Incidence of adverse events, including hospitalizations due to hypo- or hyperglycemia, or complications of diabetes.

d) Behavioral outcomes, including diet, physical activity, foot care, tobacco and alcohol consumption.

e) Costs of implementation of the intervention elements

f) Participant satisfaction with the individual intervention elements, including self-management

g) Differences between the country sites, in regard to baseline context infrastructure for prevention and management of T2D

h) Degree of implementation of intervention elements in each country, and differences between country sites informed by site-specific process evaluations

i) Effect of the interventions on perceptions towards diabetes, life style measures including physical activity, dietary behavior, etc.

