5. Similarly, for the degree of implementation of the intervention elements in each country, and differences between the country sites, we will compare the process evaluation variables/ indicators regarding ways in which program services and goods are provided (i.e. deviations) using the t-test statistic or the equivalent non-parametric test. For categorical context variables we will use the chi-square test statistic.
6. To compare changes in participant perceptions towards diabetes, physical activity, dietary behavior; and changes within contexts, as a result of implementing the intervention elements; we use multivariable linear regression mixed effects modeling with a random intercept, unstructured correlation matrix and robust standard errors, to evaluate changes over time in these outcomes of interest in relation to the assigned study arm. Visit month (categorical) at which the outcome is measured, study arm would be included in the model as fixed effects. The null hypothesis to be tested in this analysis would be that the mean changes at all the post-baseline visit months are equal between the treatment groups. The alternative hypothesis would be that the mean changes are not equal at, at least one post-baseline visit month.

We recognize that since sample size calculations for this trial were not based on the secondary outcomes, lack of significant differences in analysis of secondary outcomes might either be true lack of differences in these outcomes, or due to the fact that the trial was not sufficiently powered to detect differences in these outcomes. Thus interpretation of findings on secondary outcomes will be done with caution in case we do not detect any differences.

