**Structure of this document**

Each part starts with a table outlining the individual tools included in that section, the sources of the same and the data collection time-points for each. A framework which explains the choice of tools is also included for parts II and III.

**Variable coding strategy and tool formats:** As far as possible, all tools have been converted to a 4-column format – s.no, questions, response and variable code. Variable coding format and characters have been chosen such that they will be accepted in different statistical software packages such as STATA, SPSS, etc. Please ensure that the codes are same for each site – to avoid any problems while merging data. If sites include additional questions to the ones in the generic format, please use different codes to the ones in the generic format.

Each response is coded as a separate variable. All variables (except ID and measurement codes) are coded with the format AAAA_00x.

*For tools that will be administered multiple times (e.g. baseline and end-line):*

- AAAA represents 2-4 alphabets representing the section. E.g. Demographic – DEM;
- 00 represents the month of data collection. E.g. Baseline will be 1, end-line will be 12; and
- x is consecutive alphabets representing question numbers in each section.
- Any sub-questions under each question will be further identified by and underscore + number + alphabet as needed (e.g. _1 or _1a)
- Sometimes additional details are needed and these are added after an underscore.
- E.g. DIET_1a is first question in section on dietary behaviour collected during baseline. When the same variable is collected at end-line, it will be DIET_12a.

*For tools that will be administered only once (e.g. either baseline or end-line):*

- AAAA represents 2-4 alphabets representing the section. E.g. Demographic – DEM;
- 00 represents the question numbers
- x represents any sub-questions under each
- E.g. ELI_2a is first sub-question under question number 2 in the section on eligibility and recruitment check. Sometimes additional details are needed and these are added after an underscore.

PART I: Basic Participant Data

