| P | Which cooking method do you usually use when preparing vegetables?  1 = Grill/Oven/Roast  2 = Fry  3 = Boil  4 = Steam  5 = Other (specify) | | └──┘  If 5, please specify  **___________________** | DIET_1p  DIET_1p_other | |
| The next questions ask about the oil or fat that is most often used for meal preparation in your household, and about meals that you eat outside a home. | | | **How often** do you use the following **oils and fats** in your household? | inst_diet3 | |
| Q | | Use the scale below:  1 = Daily  2 = 5-6 days per week  3 = 2-4 days per week  4 = 1-2 days per week  5 = 1-3 days per month  6 = Occasionally, usually less than once a month  7 = Never  Don’t know 777 | 1. Vegetable oil └──┘ 2. Lard or suet └──┘ 3. Butter or ghee └──┘ 4. Margarine └──┘ 5. Mixed butter + oil combination └──┘ 6. Other └──┘If Other, specify below   Other, please specify  ____________________________ | DIET_1q_1-6 | |
|  |  |  |  | DIET_1q_other | |
| R | | On average, how often do you eat meals that were **not prepared at a home**? (By meal, we mean breakfast, lunch or dinner)  1 = Daily = 1  2 = 5-6 days per week  3 = 2-4 days per week  4 = 1-2 days per week  5 = 1-3 days per month  6 = Occasionally, usually less than once a month  7 = Never  Don’t know 777 | └──┘ | DIET_1r | |
| S | | In a typical week, on how many days do you drink **sugar-sweetened beverages** (such as sodas, and other non-carbonated commercially prepared fruit drinks)?  Don’t know 777 | Number of days└─┴─┘ *If zero, go to SECTION 6* | DIET_1s | |
| T | | How many servings of **sweetened non-carbonated drinks** (ready to drink diluted cordials and syrups/commercially prepared sweetened fruit drinks) do you drink on a typical day? | | inst_diet2a | |

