| B | On how many of the last SEVEN DAYS did you do **moderate activities** for **at least 30 minutes**, such as recreational swimming; gardening; heavy cleaning such as washing windows, vacuuming, sweeping or mopping; brisk walking; biking at moderate pace; etc.?  0 1 2 3 4 5 6 7 | └──┘ | PA_1b |

| **SECTION 7: BEHAVIOURAL MEASURES – TOBACCO USE** | | | |
| --- | --- | --- | --- |
| **S.NO:** | **Question** | **Response** | **Code** |
| A | Have you used any tobacco products, such as cigarettes, cigars, pipes, chewing tobacco or snuff/snus in the last 7 days?  1. Daily  2. Less than daily  3. Never  **If ‘never’, SKIP to SECTION 8** | **└──┘** | TOB_1a |
| B | During any visit to a doctor or other health worker in the PAST 12 MONTHS, were you **advised to quit** using tobacco?  Yes = 1  No = 0  Zero visits during the past 12 months = 3 | **└──┘** | TOB_1b |

| **SECTION 8: BEHAVIOURAL MEASURES – ALCOHOL CONSUMPTION** | | | |
| --- | --- | --- | --- |
| **S.NO:** | **Question** | **Response** | **Code** |
| A | During the PAST MONTH, **how frequently** have you had at least one standard alcoholic drink? *(USE SHOWCARD 6)*  1 = Daily = 1  2 = 5-6 days per week  3 = 2-4 days per week  4 = 1-2 days per week  5 = 1-3 days per month  6 = Occasionally, usually less than once a month  7 = Never | **└──┘** | ALC_1a |

| **SECTION 9: OTHER BEHAVIOURAL MEASURES – FOOT CARE**  **For participants with pre-diabetes, SKIP to SECTION 10** | | | |
| --- | --- | --- | --- |
| **S.NO:** | **Question** | **Response** | **Code** |
| A | On how many of the last SEVEN DAYS did you check your feet for sore/ulcers?  0 1 2 3 4 5 6 7 | **└──┘** | FOOT_1a |

| **SECTION 10: BIOCHEMICAL** | | | |
| --- | --- | --- | --- |
| **S.NO:** | **Question** | **Response** | **Code** |
| **BIOCHEMICAL – FPG** | | | |
| A | During the past 12 hours have you had anything to eat or drink other than plain water  Yes = 1  No = 0  *(To be asked when collecting FPG for diagnosis/recruitment)* | **└──┘** | FPG_1a |
|  | If yes, do not proceed |  | inst_fpg1 |
| B | Choose the units appropriate for the device measuring the fasting blood glucose  *(Essential that fasting sample collected, do not proceed if participant has not fasted)* | 1. mmol/L  2. mg/dL | FPG_1b_opt |
|  | Fasting blood glucose measure (mmol/L) | └─┴─┘**. └─┘**mmol/L | FPG_1b |
|  | Fasting blood glucose measure (mg/dL) | └─┴─┴─┘**. └─┘**mg/dL | FPG_1b_units |
| **BIOCHEMICAL – HBA1C** | | | |

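### The frequency scale used for alcohol, fat use and meals not prepared at a home gives 2 days per week two valid codes, so an unchanged respondent can be recorded as changed

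*Protocol*

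**What the plan says.** The scale appears three times in Part I of the data collection tools. Section 5 (Diet), item Q, on oils and fats, reads "Use the scale below: 1 = Daily 2 = 5-6 days per week 3 = 2-4 days per week 4 = 1-2 days per week". Item R of the same section, on meals not prepared at a home, reads "1 = Daily = 1 2 = 5-6 days per week 3 = 2-4 days per week 4 = 1-2 days per week". Section 8 (Alcohol consumption), item A, carries the same two lines: "3 = 2-4 days per week 4 = 1-2 days per week". The scale then continues "5 = 1-3 days per month 6 = Occasionally, usually less than once a month", with code 7 for never.

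None of the three items has a rule for 2 days per week. Show card 6, used with the alcohol item, defines only the size of a standard drink. The tool's log of changes does not touch these categories, and the instructions to site teams ask sites not to alter the codes.

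Section 3.9 lists as secondary outcome (d): "Behavioral outcomes, including diet, physical activity, foot care, tobacco and alcohol consumption". Table 15 (Section 3.8) and Table 1 of Part I schedule these measures at baseline and at month 12 (end-line). The coding section of the tools confirms that an item is repeated under a new month number: "When the same variable is collected at end-line, it will be DIET_12a".

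**The concern.** The answer categories of a repeated item should be mutually exclusive, so that an unchanged habit gets the same code each time. Here one weekly frequency has two correct codes. A respondent who drinks 2 days per week throughout may be coded 3 at baseline and 4 at month 12, or the reverse, and would look like someone whose drinking had moved by one step.

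Alcohol is the most exposed, because ALC_1a is its only item and no second question can settle an ambiguous answer. DIET_1q has six sub-items, so eight variables carry the overlap in all (6 + 1 + 1). The loss cannot be repaired afterwards: once a 3 is on file, nobody can tell whether it stood for 2 days or for 3-4, and a recorded 4 may stand for 1 day or for 2.

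**Working it through.** No sample-size, power or alpha figure is involved, and the plan gives no figure of its own to reproduce. Section 3.13.2 notes that "sample size calculations for this trial were not based on the secondary outcomes".

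**Step 1: are the categories exclusive and exhaustive?** Each whole number of days per week is mapped to the printed codes.

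| Days per week | Valid code(s) |
| --- | --- |
| 7 | 1 |
| 5-6 | 2 |
| 3-4 | 3 |
| 2 | 3 or 4 |
| 1 | 4 |

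There is no gap between 1 and 7 days. The only double assignment is at 2 days. The next band down, 1-3 days per month, does not overlap code 4.

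**Step 2: chance of a spurious change for one person.** Take someone truly at 2 days per week at both visits. Let p be the chance that code 3 is recorded, the same at each visit and independent between visits (an assumption; the documents give no p). The chance that the two codes differ is 2p(1-p):

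- p = 0 or 1: 0
- p = 0.1 or 0.9: 2 × 0.1 × 0.9 = 0.18
- p = 0.3 or 0.7: 2 × 0.3 × 0.7 = 0.42
- p = 0.5: 2 × 0.5 × 0.5 = 0.50, the maximum

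**Step 3: share of all respondents.** The documents do not say how many respondents are at 2 days per week. Assume 5-20%:

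| p | Chance of differing codes | At 5% | At 20% |
| --- | --- | --- | --- |
| 0 or 1 | 0 | 0% | 0% |
| 0.1 or 0.9 | 0.18 | 0.9% | 3.6% |
| 0.3 or 0.7 | 0.42 | 2.1% | 8.4% |
| 0.5 | 0.50 | 2.5% | 10% |

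The range is 0-10% of respondents for a given item.

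**Step 4: what is not affected.** In Section 5, items A, C, E, G, I, K and S record a number of days. Physical activity (Section 6) and foot care (Section 9) use 0-7 day counts. Tobacco (Section 7) has its own three-level scale. None of these overlaps.

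**Step 5: after the fix.** With code 3 as 3-4 days and code 4 as 1-2 days, every whole number from 1 to 7 has exactly one code, and the change caused by ambiguity falls to 0.

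**The case against.** The strongest reply is that this is a wording slip at one frequency value on a coarse self-report scale. A steady habit, such as taking the first option that fits, produces no spurious change at all. The protocol fixes no derived variable or category contrast for ALC_1a, and the change model in Section 3.13.2, item 6, names perceptions towards diabetes, physical activity and dietary behaviour but not alcohol. If alcohol were split at a point away from the boundary between codes 3 and 4, the overlap would do no harm. All of this stands. It keeps the point minor and makes the harm conditional, but it does not remove the double code or supply a rule for it.

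A reader might infer three stronger things that the documents do not support.

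- *Bias between arms.* The arm code is on the form, and South Africa has two clusters for two arms, so a coding habit specific to one facility would coincide with arm there. But nothing shows that habits differ. The tools do not say whether the respondent or the interviewer resolves the choice. In Sweden (Section 3.6.3), zones within each centre's catchment were allocated, so the facility alone does not fix the arm.
- *A guaranteed minimum of misclassification.* A range of 2.5-10% holds only at p = 0.5, the worst case under the stated model; the lower end is 0.
- *Damage to dietary behaviour as a whole.* Only items Q and R are touched.

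**Conclusion.** The point holds as a minor but definite error in an instrument that the trial uses. Codes 3 and 4 overlap at exactly 2 days per week in ALC_1a, DIET_1q and DIET_1r, and nothing in the document resolves it. The consequence is possible one-category misclassification of change in parts of secondary outcome (d).

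Its size cannot be computed from the documents. The 0-10% range rests on an assumed 5-20% of respondents at 2 days per week, and on the same independent coding tendency at both visits; a change of convention between visits lies outside that range. If coding is unrelated to site or cluster, the effect is added noise. The HbA1c primary outcomes are not involved.

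**What to change.** Relabel code 3 as 3-4 days per week in ALC_1a, DIET_1q and DIET_1r, leave the other codes as they are, and use the same version at baseline and month 12. The numbering does not change, so variable names and merging across sites are unaffected. Because sites are told not to alter the codes, the correction should be issued centrally and carried into the translated tools. The cost is one label in three items.

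If baseline data have already been collected, do not change the label for month 12 alone. Keep the codes as collected and merge 3 and 4 into a single band of 1-4 days per week at both visits in the analysis of these items. That removes the ambiguity, but 1 day can then no longer be told from 4, and the four bands at weekly or more become three. The loss is real and should be stated when the results are reported.

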**BREAK data collection HERE, according to instructions on page 5**

PART II: Intervention process measures (mainly based on Self Determination Theory)

The broad principles of the intervention are based on Self-determination theory (SDT). Therefore, the evaluation of theoretical components is also based on the SDT framework. Figure 1 shows a simplified version of the SDT framework. This section of the document contains tools to measure each of these components.

**
[figure not shown]
**

*Figure 1: Components of SDT as measured by the evaluation tools in this section*

**Table 2: Details of tools, sources and data collection points for Part II**

| Questionnaires | Source | BL | M2-11 | EL |
| --- | --- | --- | --- | --- |
| **Social Support** | GACD diabetes data dictionary | X |  | X |
| **Sources of support** | Kerala Diabetes Prevention Programme (KDPP) | X |  | X |
| **Self-efficacy** | Pilvikki et al: The perceived self-efficacy scale  <http://www.ncbi.nlm.nih.gov/pubmed/23740266> | X |  | X |
| **Autonomy support** | Health care climate questionnaire  (see website self-determination theory) | X |  | X |
| **Self-regulation** | Treatment Self-Regulation Questionnaire (TSRQ)  (see website self-determination theory) | X |  | X |
| **Psychological Adjustment** | Torres et al: <http://www.ncbi.nlm.nih.gov/pubmed/16341399>  Rodrigues et al: <http://www.ncbi.nlm.nih.gov/pubmed/19820852> | X |  | X |
| **Quality of Life & Stress*** | - GACD diabetes data dictionary  - The 2-item Diabetes Distress Screening Scale | X |  | X |
| **Treatment Satisfaction*** | SMART2D | X |  | X |
| **Knowledge about diabetes** | Garcia et al: <http://care.diabetesjournals.org/content/24/1/16> | X |  | X |

*** The quality of life and stress and Diabetes treatment satisfaction questionnaires do not belong with SDT. However, they do measure process outcomes and use the Likert scale responses. We therefore felt that participants will be able to respond easier in this section as responses are along similar lines to the other SDT-related tools.

| **SECTION 12: SOCIAL SUPPORT** | | | |
| --- | --- | --- | --- |
| **S.No:** | **Questions** | **Response** | **Code** |
| A | Intro: **We want to understand to what extent people close to you (friends, family or relatives) have helped you to do physical activity.** | |  |
|  | How often have people close to you (friends, family or relatives) **exercised with you**?  1= Never  2= less than once a week  3= once a week  4= more than once a week  888= no answer/not applicable | └──┘ | SUP_a_exercised |
|  | How often have people close to you (friends, family or relatives) **encouraged you to exercise**?  1= Never  2= less than once a week  3= once a week  4= more than once a week  888= no answer/not applicable | └──┘ | SUP_a_encouraged |
|  | How often have people close to you (friends, family or relatives) **changed their schedule so you could exercise together**?  1= Never  2= less than once a week  3= once a week  4= more than once a week  888= no answer/not applicable | └──┘ | SUP_a_changed |
|  | How often have people close to you (friends, family or relatives) **discussed exercising with you**?  1= Never  2= less than once a week  3= once a week  4= more than once a week  888= no answer/not applicable | └──┘ | SUP_a_discussed |
|  | How often have people close to you (friends, family or relatives) **helped you with exercising on special occasions such as holidays, feasts, family gatherings**?  1= Never  2= less than once a week  3= once a week  4= more than once a week  888= no answer/not applicable | └──┘ | SUP_a_planned |
| B | Intro: **We want to understand to what extent people close to you (friends, family or relatives) have helped you to maintain a healthy diet.** | |  |
|  | How often have people close to you (friends, family or relatives) **eaten healthy food with you**?  1= Never  2= less than once a week  3= once a week  4= more than once a week  888= no answer/not applicable | └──┘ | SUP_b_eaten |
|  | How often have people close to you (friends, family or relatives) **encouraged you to stick with your healthy diet**?  1= Never  2= less than once a week  3= once a week  4= more than once a week  888= no answer/not applicable | └──┘ | SUP_b_encouraged |
|  | How often have people close to you (friends, family or relatives) **changed their eating habits into healthier so you could eat the same foods**?  1= Never  2= less than once a week  3= once a week  4= more than once a week  888= no answer/not applicable | └──┘ | SUP_b_changed |
|  | How often have people close to you (friends, family or relatives) **discussed healthy eating with you**?  1= Never  2= less than once a week  3= once a week  4= more than once a week  888= no answer/not applicable | └──┘ | SUP_b_discussed |
|  | How often have people close to you (friends, family or relatives) **helped you with eating healthy food on special occasions such as holidays, feasts, family gatherings**?  1= Never  2= less than once a week  3= once a week  4= more than once a week  888= no answer/not applicable | └──┘ | SUP_b_planned |

| **SECTION 13: SOURCES of SUPPORT / ENCOURAGEMENT** | | | | |
| --- | --- | --- | --- | --- |
| **Instruction for data collectors on LIKERT scales:**  In this section, the 2 step approach needs to be used:  **Give SHOWCARD 7 to the participant to help them through the responses**  Ask the question in two parts:   1. Ask the participant the specific question as written below 🡪Participant answers: Yes/neutral/no   Data collector asks: ‘do you strongly or moderately (dis)agree’ | | | inst_sos1 | |
|  | **Sources of Support** | **Response** | | **Code** |
| **For participants with pre-diabetes, SKIP to B.** | | | | |
| A | Intro: We want to know about different groups of people if they are helping you with your diabetes management. Diabetes management can include various things like taking medication, helping with exercise, maintaining a healthy diet, accompanying you to the health centre, etc.  *Clarification for data-collectors: The meaning of “help” relates to encouragement, information sharing, sharing experiences, etc..*  *Instructions:’ Not applicable’ to be used only for the following items, if they are not available at the time of the survey: peer leaders, peer groups, community link team (SA: CHW) and care companions.* | | |  |
|  | Do **family members** help you with your diabetes management?  1 Strongly disagree  2 Disagree  3 Neutral  4 Agree  5 Strongly agree  888 Not applicable | └──┘ | | SOS_1a_family |
|  | Do **friends** help you with your diabetes management?  1 Strongly disagree  2 Disagree  3 Neutral  4 Agree  5 Strongly agree  888 Not applicable | └──┘ | | SOS_1a_friends |
|  | Does the **health centre** help you with your diabetes management?  1 Strongly disagree  2 Disagree  3 Neutral  4 Agree  5 Strongly agree  888 Not applicable | └──┘ | | SOS_1a_hc |
| **For participants with diabetes, SKIP to Section 14** | | | | |
| B | Intro: We want to know about different groups of people if they are helping you with maintaining a healthier lifestyle. A healthier lifestyle can include various things like helping you to exercise, eat well, stop smoking, etc.  *Clarification for data-collectors: The meaning of “help” relates to encouragement, information sharing, sharing experiences, etc..*  *~~Instructions:’ Not applicable’ to be used only for the following items, if they are not available at the time of the survey: peer leaders, peer groups, community link team (SA: CHW) and care companions.~~* | | |  |
|  | Do **family members** help you with your healthy lifestyle such as exercising and eating well?  1 Strongly disagree  2 Disagree  3 Neutral  4 Agree  5 Strongly agree  888 Not applicable | └──┘ | | SOS_1b_family |
|  | Do **friends** help you with your healthy lifestyle such as exercising and eating well?  1 Strongly disagree  2 Disagree  3 Neutral  4 Agree  5 Strongly agree  888 Not applicable | └──┘ | | SOS_1b_friends |
|  | Does the **health centre** help you with your healthy lifestyle such as exercising and eating well?  1 Strongly disagree  2 Disagree  3 Neutral  4 Agree  5 Strongly agree  888 Not applicable | └──┘ | | SOS_1b_hc |

| **SECTION 14: SELF-EFFICACY** | | | |
| --- | --- | --- | --- |
| **Instruction for data collectors on LIKERT scales:**  In this section, the 2 step approach needs to be used:  **Give SHOWCARD 7 to the participant to help them through the responses**  Ask the question in two parts:   1. Ask the participant the specific question as written below 🡪Participant answers: Yes/neutral/no   Data collector asks: ‘do you strongly or moderately (dis)agree’ | | | inst_eff1 |
| Intro: **We want to know if you can maintain a healthy diet ~~and do physical activity~~ under specific circumstances.** | | | |
| **S.NO:** | **Question** | **Response** | **Code** |
| A | Do you think you can maintain a healthy diet **even if you need to change how you cook at home**?  1 Strongly disagree  2 Disagree  3 Neutral  4 Agree  5 Strongly agree  888 Not applicable | └──┘ | EFF_1a |
| B | Do you think you can maintain a healthy diet **even if you are not used to the taste of these foods**?  1 Strongly disagree  2 Disagree  3 Neutral  4 Agree  5 Strongly agree  888 Not applicable | └──┘ | EFF_1b |
| C | Do you think you can maintain a healthy diet **even if this means that you have to eat less**?  1 Strongly disagree  2 Disagree  3 Neutral  4 Agree  5 Strongly agree  888 Not applicable | └──┘ | EFF_1c |
| D | Do you think you can maintain a healthy diet **even if your family or friends don’t help you**?  1 Strongly disagree  2 Disagree  3 Neutral  4 Agree  5 Strongly agree  888 Not applicable | └──┘ | EFF_1d |
| E | Do you think you can maintain a healthy **diet even if you would have to pay more for it**?  1 Strongly disagree  2 Disagree  3 Neutral  4 Agree  5 Strongly agree  888 Not applicable | └──┘ | EFF_1e |
| F | Do you think you can maintain a healthy diet **even if others around you eat unhealthy food**?  1 Strongly disagree  2 Disagree  3 Neutral  4 Agree  5 Strongly agree  888 Not applicable | └──┘ | EFF_1f |
| **We want to know if you can ~~maintain a healthy diet and~~ do physical activity under specific circumstances.** | | | |
| G | Do you think you can be physically active **even during holidays, weddings or other special events**?  1 Strongly disagree  2 Disagree  3 Neutral  4 Agree  5 Strongly agree  888 Not applicable | └──┘ | EFF_1g |
| H | Do you think you can be physically active **even if your family does not encourage you to be physically activity**?  1 Strongly disagree  2 Disagree  3 Neutral  4 Agree  5 Strongly agree  888 Not applicable | └──┘ | EFF_1h |
| I | Do you think you can be physically active **even if you think it is not the best weather for doing sports**?  1 Strongly disagree  2 Disagree  3 Neutral  4 Agree  5 Strongly agree  888 Not applicable | └──┘ | EFF_1i |
| J | Do you think you can be physically active **even if you are in a place with no exercise facilities or safe roads for walking**?  (probing ‘for instance at home or at work or in another way’)    1 Strongly disagree  2 Disagree  3 Neutral  4 Agree  5 Strongly agree  888 Not applicable | └──┘ | EFF_1j |
| K | Do you think you can be physically active **even if you have health problems?**  1 Strongly disagree  2 Disagree  3 Neutral  4 Agree  5 Strongly agree  888 Not applicable | └──┘ | EFF_1k |
| L | Do you think you can be physically active **even if no other people around you are doing exercise or walking**?  1 Strongly disagree  2 Disagree  3 Neutral  4 Agree  5 Strongly agree  888 Not applicable | └──┘ | EFF_1l |

| **SECTION 15: AUTONOMY SUPPORT** | |
| --- | --- |
| **Instruction for data collectors on LIKERT scales:**  In this section, the 2 step approach needs to be used:  **Give SHOWCARD 7 to the participant to help them through the responses**  Ask the question in two parts:   1. Ask the participant the specific question as written below 🡪Participant answers: Yes/neutral/no   Data collector asks: ‘do you strongly or moderately (dis)agree’ | inst_aus1 |
| Intro: We want to know how the doctors and nurses working at the health centre or clinic treat you regarding your diabetes/pre-diabetes management. Diabetes management can include various things like taking medication, exercising, following a healthy diet, etc. Pre-diabetes management can include various things like exercising, following a healthy diet, etc.  Please respond according to the condition you have, either diabetes or pre-diabetes: | |

| **S.NO** | **Question** | **Response** | **Code** |
| --- | --- | --- | --- |
| A | Do you feel that the nurses and doctors at the health centre or clinic **give you choices and options *about your diabetes / pre-diabetes management****?*  1 Strongly disagree  2 Disagree  3 Neutral  4 Agree  5 Strongly agree  888 Not applicable | └──┘ | AUS_1a |

| B | Do you feel that the nurses and doctors at the health centre or clinic **understand how you see things *regarding* *your diabetes / pre-diabetes management****?*  1 Strongly disagree  2 Disagree  3 Neutral  4 Agree  5 Strongly agree  888 Not applicable | └──┘ | AUS_1b |
| --- | --- | --- | --- |
| C | Do you feel that the nurses and doctors at the health centre or clinic **make you feel able to change *your diabetes / pre-diabetes management****?*  1 Strongly disagree  2 Disagree  3 Neutral  4 Agree  5 Strongly agree  888 Not applicable | └──┘ | AUS_1c |
| D | Do you feel that the nurses and doctors at the health centre or clinic **listen to how you would like to do things regarding *your diabetes / pre-diabetes management***?  1 Strongly disagree  2 Disagree  3 Neutral  4 Agree  5 Strongly agree  888 Not applicable | └──┘ | AUS_1d |
| E | Do you feel that the nurses and doctors at the health centre or clinic **encourage you to ask questions about *your diabetes / pre-diabetes management***?  1 Strongly disagree  2 Disagree  3 Neutral  4 Agree  5 Strongly agree  888 Not applicable | └──┘ | AUS_1e |
| F | Do you feel that the nurses and doctors at the health centre or clinic **try to understand how you see *your diabetes / pre-diabetes management,* before suggesting a different treatment**?  1 Strongly disagree  2 Disagree  3 Neutral  4 Agree  5 Strongly agree  888 Not applicable | └──┘ | AUS_1f |

| **SECTION 16: SELF-REGULATION** | | | |
| --- | --- | --- | --- |
| **Instruction for data collectors on LIKERT scales:**  In this section, the 2 step approach needs to be used:  **Give SHOWCARD 7 to the participant to help them through the responses**  Ask the question in two parts:   1. Ask the participant the specific question as written below 🡪Participant answers: Yes/neutral/no   Data collector asks: ‘do you strongly or moderately (dis)agree’ | | | inst_sreg1 |
| **S.No.** | **Question** | **Response** | **Code** |
|  | Intro: Think for a moment about the **reasons** why you actually would follow a healthy diet: why would you do this?  (*Instructions: give the patient a couple of seconds to think about it*).  We will now present possible reasons why you may follow a healthy diet. Please agree or disagree, using the options provided. | |  |
| A | Would you maintain a healthy diet **because** **you personally believe it is the best thing for your health**?  1 Strongly disagree  2 Disagree  3 Neutral  4 Agree  5 Strongly agree  888 Not applicable | └──┘ | SREG_1a |
| B | Would you maintain a healthy diet **because** **you'd feel bad about yourself if you didn't**?  1 Strongly disagree  2 Disagree  3 Neutral  4 Agree  5 Strongly agree  888 Not applicable | └──┘ | SREG_1b |
| C | Would you maintain a healthy diet **because** **you feel pressure from others to do it?**  1 Strongly disagree  2 Disagree  3 Neutral  4 Agree  5 Strongly agree  888 Not applicable | └──┘ | SREG_1c |
| D | Would you maintain a healthy diet **because** **others would be upset with you if you didn't**?  1 Strongly disagree  2 Disagree  3 Neutral  4 Agree  5 Strongly agree  888 Not applicable | └──┘ | SREG_1d |
| E | Would you maintain a healthy diet **because** **it is very important for being as healthy as possible**?  1 Strongly disagree  2 Disagree  3 Neutral  4 Agree  5 Strongly agree  888 Not applicable | └──┘ | SREG_1e |
| F | Would you maintain a healthy diet **because** **you would feel guilty or ashamed of yourself if you didn’t**?  1 Strongly disagree  2 Disagree  3 Neutral  4 Agree  5 Strongly agree  888 Not applicable | └──┘ | SREG_1f |
| G | Would you maintain a healthy diet **because** **you feel that you want to take responsibility for your own health**?  1 Strongly disagree  2 Disagree  3 Neutral  4 Agree  5 Strongly agree  888 Not applicable | └──┘ | SREG_1g |
| H | Would you maintain a healthy diet **because it is an important choice you really want to make**?  1 Strongly disagree  2 Disagree  3 Neutral  4 Agree  5 Strongly agree  888 Not applicable | └──┘ | SREG_1h |
|  | Intro: Think for a moment about the **reasons** why you actually would do physical exercise: why would you do this?  (*Instructions: give the patient a couple of seconds to think about it*).  We will now present possible reasons why you may do physical exercise. Please agree or disagree, using the options provided. | |  |
| I | Would you do physical exercise **because** **you personally believe it is the best thing for your health**?  1 Strongly disagree  2 Disagree  3 Neutral  4 Agree  5 Strongly agree  888 Not applicable | └──┘ | SREG_1i |
| J | Would you do physical exercise **because** **you'd feel bad about yourself if you didn't**?  1 Strongly disagree  2 Disagree  3 Neutral  4 Agree  5 Strongly agree  888 Not applicable | └──┘ | SREG_1j |
| K | Would you do physical exercise **because** **you feel pressure from others to do it**?  1 Strongly disagree  2 Disagree  3 Neutral  4 Agree  5 Strongly agree  888 Not applicable | └──┘ | SREG_1k |
| L | Would you do physical exercise **because** **others would be upset with you if you didn't**?  1 Strongly disagree  2 Disagree  3 Neutral  4 Agree  5 Strongly agree  888 Not applicable | └──┘ | SREG_1l |
| M | Would you do physical exercise **because it is very important for being as healthy as possible**?  1 Strongly disagree  2 Disagree  3 Neutral  4 Agree  5 Strongly agree  888 Not applicable | └──┘ | SREG_1m |
| N | Would you do physical exercise **because** **you would feel guilty or ashamed of yourself if you didn’t**?  1 Strongly disagree  2 Disagree  3 Neutral  4 Agree  5 Strongly agree  888 Not applicable | └──┘ | SREG_1n |
| O | Would you do physical exercise **because you feel that you want to take responsibility for your own health**?  1 Strongly disagree  2 Disagree  3 Neutral  4 Agree  5 Strongly agree  888 Not applicable | └──┘ | SREG_1o |
| P | Would you do physical exercise **because** **it is an important choice you really want to make**?  1 Strongly disagree  2 Disagree  3 Neutral  4 Agree  5 Strongly agree  888 Not applicable | └──┘ | SREG_1p |

| **SECTION 17: PSYCHOLOGICAL ADJUSTMENT** | | | |
| --- | --- | --- | --- |
